#### Quality control egg counting procedure

A predefined, randomly selected subset of samples (10% of the total number of samples) will be re-evaluated by each of the three egg count methods. To this end, a senior researcher, who is blinded to the initial FECs, will re-count STH eggs across all three egg count methods. A third examiner will re-count STH eggs in case of discrepancies. Discrepancies are defined as (i) false negatives/positives, (ii) difference in egg counts >10 when the total number of eggs counted ≤100 or (iii) difference in egg counts >20% when more than 100 eggs are counted [24]. A detailed SOP on the performance of quality control for the egg counting methods is provided in the supplementary information (S6 Info).

### DNA-based methods

#### Stool preservation and DNA extraction

After performing the egg counting methods, stool samples will be preserved. At baseline, only those samples in which a sufficient number of eggs are counted for at least one STH species will be preserved (duplicate Kato-Katz thick smear: 13 eggs; Mini-FLOTAC: 15 eggs). At follow-up, all samples will be preserved, and this regardless of the number of STH eggs found. For each sample, 2 subsamples of 0.5 g will be preserved in 1 ml of absolute ethanol. A detailed SOP on sample preservation is provided in the supplementary information (S7 Info). Preserved samples will be stored in sample boxes at room temperature and shipped to Belgium for DNA extraction and subsequent molecular analysis. The DNA extraction protocol will be run on the automated QiaSymphony using a preceding mechanical lysis step by means of bead beating. This DNA protocol maximizes STH DNA yield from stool (Ayana et al, in preparation). DNA extraction will be performed at Ghent University (Belgium) and Elizabeth Tweesteden Hospital (The Netherlands). S8 Info provides a detailed SOP on DNA extraction.

#### qPCR

All DNA extracts will be analyzed for the presence of *A*. *lumbricoides*, *T*. *trichiura*, *N*. *americanus* and *A*. *duodenale* DNA using qPCR assays previously described [37, 63, 64]. S9 Info provides a detailed SOP on how we will perform the qPCR. The output of the qPCR analysis will be expressed in genome equivalents (GE) per ml DNA extract.

#### Pyrosequencing

In two subsets of the DNA samples, we will apply a previously described pyrosequencing protocol [30, 52] to determine frequency of mutant SNPs in the three codons of the ß-tubulin associated with BZ resistance. The first subset will consist only of baseline DNA samples, and will be used to assess the association between drug pressure history and the corresponding frequency of mutant SNPs linked to BZ resistance. Per study site, 60 baseline DNA samples positive for each STH species (*Ascaris*, *Trichuris* and hookworm) will be randomly selected from the available baseline DNA samples. To avoid these samples representing one school or one level of individual response to ALB, selection of the samples will be proportionately to the total number of cases per school and individual drug response (Table 3).

**Table 3 pntd.0006912.t003:** Classification of the individual response to a single oral dose 400 mg ALB against STH based on the individual egg reduction rate (iERR).

STH	Cured	Responder	Poor responder	Non-responder
***Ascaris***	iERR = 100%	iERR ≥ 95%	85% ≤ iERR < 95%	iERR < 85%
***Trichuris***	iERR = 100%	iERR ≥ 50%	40% ≤ iERR < 50%	iERR < 40%
**Hookworms**	iERR = 100%	iERR ≥ 90%	80% ≤ iERR < 90%	iERR < 80%

We will use a second set of DNA samples to assess the association between individual responses to ALB by pyrosequencing the ß-tubulin gene. At each site, samples from at least 30 participants who were cured (baseline samples only) and from at least 30 participants who were still excreting eggs at follow-up (both baseline and follow-up samples) will be selected for each STH species separately. Participants which still excreted eggs will be stratified, into ‘responders’, ‘poor responders’ and ‘non-responders’. This stratification will be based on WHO thresholds used for classifying the efficacy into ‘satisfactory’ (‘responders’), ‘doubtful’ (‘poor responders’) and ‘reduced’ (‘non-responders’) [27] (Table 3). A total of 10 participants will be randomly selected for each stratum. Total DNA will be extracted from these stool samples and sent for pyrosequencing at McGill University (Canada).

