### Assess associations between frequency of SNPs linked to BZ resistance measured by pyrosequencing and history of drug pressure and drug efficacy

To assess the association between mutant SNPs linked to BZ resistance and history of drug pressure, a permutation test will be applied to evaluate differences in frequency of mutant SNPs linked to BZ in the baseline samples across the study sites. Tukey’s method will be applied for pair-wise comparisons between the study sites.

To assess the association between mutant SNPs linked to BZ resistance and drug efficacy, a permutation test will be applied to evaluate any difference in frequency of mutant SNPs linked to BZ across the four levels of individual response to ALB (Table 3). Tukey’s method will be applied for pair-wise comparisons between the four levels of individual response.

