By standardizing the drug efficacy trials (e.g., egg count method, follow-up period, anthelmintic drug and statistical analysis) and strategically selecting the study sites (varying drug pressure history, and hence possibly differences in drug efficacy), we hope to provide complementary insights into SNPs in the β-tubulin gene as a marker for BZ resistance in human STHs. If these SNPs play a role in AR, we expect an increase in frequency in mutant SNPs in STHs as a function of increased drug pressure history and decreased individual response to treatment. However, this molecular part of the study may face some challenges, which may impede a straightforward interpretation of the results. First, if the expected trends in SNPs are not detected, it is not possible to completely exclude them as a marker for BZ resistance. Furthermore, it could also indicate that resistance to BZ has not yet emerged, which would also jeopardize any downstream objectives (e.g. comparison of pyrosequencing and LAMP for the assessment of SNPs linked to BZ resistance and assessing pooling samples as a cost-saving strategy to determine the frequency of SNPs linked to BZ resistance). It is also important to note that any observed trends would only suggest an association rather than causal relationship. Second, it remains unclear whether we will be able to select the number of cases per level of individual response for each of the different STH species. Finally, the classification of the individual response is based on the outcome of imperfect tests (sub-optimal sensitivity), further complicating the interpretation.

To conclude, the combined results of this study are expected to answer a number of outstanding questions with regards to how to best monitor drug efficacy and measure AR in populations that are being subjected to PC for STH infections. The results could be translated into novel recommendations for the scientific community on what is the best diagnostic method to assess drug efficacy in ongoing control programs and will create the basis to set up a robust surveillance system.

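### The SNP-versus-response test is assigned to the second pyrosequencing set only, although the first set's baseline samples are sequenced and already classed by response and could be pooled into it

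*Protocol article*

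**What the plan says.** All references are to the protocol article.

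- **First set (Pyrosequencing).** Its purpose is stated as "The first subset will consist only of baseline DNA samples, and will be used to assess the association between drug pressure history" and the matching SNP frequency. Its size is "Per study site, 60 baseline DNA samples positive for each STH species". To avoid one school or one response level dominating, "selection of the samples will be proportionately to the total number of cases per school and individual drug response", with the classes taken from Table 3.
- **Second set (Pyrosequencing).** "We will use a second set of DNA samples to assess the association between individual responses to ALB". Per site and species it takes "samples from at least 30 participants who were cured (baseline samples only") and at least 30 still excreting eggs, 10 from each of the responder, poor-responder and non-responder classes. The egg-excreting children have both baseline and follow-up samples sequenced.
- **Analysis (section on associations between SNP frequency, drug pressure and drug efficacy).** A permutation test will "evaluate any difference in frequency of mutant SNPs linked to BZ across the four levels of individual response to ALB", followed by Tukey pair-wise comparisons. No sample set is named.
- **Discussion.** The authors concede that "it remains unclear whether we will be able to select the number of cases per level of individual response" for each species.

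**The concern.** The response association is one of the two trends by which the Discussion says SNPs would be judged as a resistance marker; the other is drug-pressure history. As assigned, it rests on 10 children per uncured class per site, or 40 per class over four sites.

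Meanwhile up to 240 further baseline samples per species go through the same assay, from the same sites, with a response class fixed before they are selected. Within a site and response class both sets are random draws from the same children, apart from the first set's proportional spread over schools. Their class mixes differ, and the first set's mix will vary between sites. A response test stratified by site can therefore take both sets. Leaving the first set out gives up information already paid for.

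**Working it through.** **1. Planned counts.** Second set: 3 × 10 = 30 egg-excreting plus 30 cured = 60 per site and species. Over four sites this is 120/40/40/40 (cured/responder/poor/non-responder) = 240. First set: 60 × 4 = 240. The article states no power for this objective, so there is none to reproduce. The 110, 100 and 12 complete cases under Sample size calculation belong to egg-reduction-rate equivalence.

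**2. Usable time point.** Cured children contribute baseline samples only, so baseline is the only time point common to all four classes. That is what the first set provides.

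**3. What pooling adds, by class.** The article does not say that the sets are disjoint, so overlap must be allowed for. With N eligible cases per site and class share p, the second set takes s = min(N·p, quota). The first set then adds on average (N·p − s) × 60/N new children per site. The shares (cured/responder/poor/non-responder) and N are assumptions. With N = 200:

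- *Trichuris*-like, 40/30/8/22. Non-responders: (44 − 10) × 0.3 = 10.2 per site, so 40 becomes about 81 over four sites. Cured: (80 − 30) × 0.3 = 15 per site, so 120 becomes 180.
- Hookworm-like, 70/20/5/5. Non-responders: (10 − 10) × 0.3 = 0, so 40 stays 40. Cured: (140 − 30) × 0.3 = 33 per site, so 120 becomes 252.
- *Ascaris*-like, 90/6/2/2. Non-responders: only 4 exist per site and all are already taken, so 16 stays 16. Cured: (180 − 30) × 0.3 = 45 per site, so 120 becomes 300.

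**4. Information for cured versus non-responder**, 1/(1/n₁ + 1/n₂):

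- *Trichuris*-like: from 1/(1/120 + 1/40) = 30.0 to 1/(1/180 + 1/81) = 55.9, a factor of 1.86.
- Hookworm-like: from 30.0 to 1/(1/252 + 1/40) = 34.5, a factor of 1.15.
- *Ascaris*-like: from 1/(1/120 + 1/16) = 14.1 to 1/(1/300 + 1/16) = 15.2, a factor of 1.08.

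**5. Power of the four-level test, by simulation.** All inputs are assumed: four sites, 150–300 cases per site, SNP frequency SD 15 points, class means 10/12/14/16% plus site differences, each child counted once, and a site-adjusted F-test standing in for permutation within site.

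| Assumed class shares | Second set only | Both sets |
|---|---|---|
| *Trichuris*-like | about 47% | 70–74% |
| Hookworm-like | 38–48% | 48–64% |
| *Ascaris*-like | 21–37% | 28–42% |

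Type I error stayed at about 3–6%.

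**6. Scarce classes.** In simulation with 150 cases per site and *Ascaris*-like shares, poor and non-responders over four sites averaged 12.0 and 12.2 with the second set alone and the same with both sets. With hookworm-like shares they went from 29.0 and 28.7 to 29.5 and 29.2. The added children fall almost wholly in classes that were already full.

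**The case against.** The best defence is that nothing in the article is wrong or contradictory. The analysis section compares the four response levels without naming a set, and which sequenced samples enter a secondary test is often settled in an analysis plan that is not shown. That limits the point to efficiency and clarity, and this much stands. It does not remove the point: the Pyrosequencing section is the only text that assigns samples to the response question, and it assigns the second set.

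The second objection is that the size of the gain depends entirely on assumed inputs. This also stands. A reader might infer that a large share of power is being lost for every species. The documents do not support that: they give no SNP variance, effect size or class shares, and the illustrated gain is small where nearly all children are cured.

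The third objection is that pooling cannot help where it is most needed. A reader might infer that the first set would repair the class shortfalls the Discussion fears. It would not: where a site has fewer than 10 children in a class, the second set already takes them all, unless it were drawn to exclude first-set children, which the article does not say.

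Finally, a reader might take the planned response test to be biased or invalid. Nothing in the documents shows that; it only uses fewer children than it could.

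**Conclusion.** The concern holds as a point of efficiency. The Pyrosequencing section reserves the response question for the second set, while the first set's baseline samples are sequenced, classed by response and usable in a site-stratified test. Under the assumptions listed, the gain in power is about 23–27 percentage points for *Trichuris*-like shares (70 − 47 to 74 − 47), about 10–16 points for hookworm-like shares (48 − 38 to 64 − 48), and about 5–7 points for *Ascaris*-like shares (42 − 37 to 28 − 21). These are illustrations, not estimates for this trial. The direction is firmer than the size: the gain is largest where many children remain uncured, and the article's expected efficacy (*Trichuris* ~65%, hookworms ~96%, *Ascaris* ~99%) suggests that *Trichuris* is that species. The doubt about filling the scarce classes remains.

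**What to change.** Keep both sets as planned, including baseline and follow-up sequencing for second-set children still excreting eggs. Then state, in the Pyrosequencing section and in the analysis section on SNP associations, that:

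- the four-level response test on baseline SNP frequency uses all distinct children with a sequenced baseline sample, both sets combined and each child counted once;
- permutation is done within site;
- the drug-pressure test uses the first set alone, since the second set's quotas distort the natural response mix.

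The article should also say whether a child may be drawn into both sets.

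Drawing the first set first and using the second only to top up short classes may look like a saving, but it should not be adopted. For *Trichuris*-like shares power would be only about 54–56%, and egg-excreting children with planned follow-up sequencing would fall from about 118–120 to 19–22 over four sites.

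The cost is a few sentences of analysis wording and the added condition of permuting within site. No extra sampling or sequencing is needed.

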#### LAMP

A previously described LAMP protocol [65] will be applied on a subset of 300 DNA samples that are withheld for pyrosequencing. The selection of these samples will be based on the frequency of SNPs linked to AR. Based on the pyrosequencing results, samples will be classified into four levels of SNP frequency, including absence of SNP linked to BZ resistance, and low, moderate and high frequency of SNPs linked to BZ resistance. The thresholds used to define the last three levels of frequency of SNPs will be based on the 1^st^ and 3^rd^ quartile of the frequency of SNP across all the samples, in which SNP linked to BZ resistance are present. Samples in which the frequency of a SNP for BZ resistance is higher than 0% but lower than the 1^st^ quartile will be classified into the low frequency group, samples in which the frequency of a SNP for BZ resistance is at least equal to the 3^rd^ quartile will be classified into the high frequency group. All other samples, in which SNPs linked to BZ resistance are found, will be classified into the moderate frequency group. For each STH species (*Ascaris*, *Trichuris*, and hookworms), 25 samples in each level of SNP frequency will be randomly selected and processed with the LAMP assay. The LAMP will be performed at McGill University (Canada) and at two study sites (Ethiopia and Tanzania).

#### Pooling stool samples for DNA-based diagnostic methods

For both qPCR and pyrosequencing/LAMP, pooled samples will be analyzed. For qPCR, aliquots of all stool samples preserved for further molecular analysis will be pooled into pools of 10, 20 and 60 individual samples. The procedure to pool stool was adapted from Mekonnen et al., [66]. A detailed SOP on sample pooling is available in supplementary information (S10 Info). For pyrosequencing and LAMP, only samples that are withheld for pyrosequencing will be pooled into pools of 10 individual samples. All downstream processes (DNA extraction extracted, qPCR and pyrosequencing/LAMP) will be performed as described in aforementioned sections.

### Cost analysis of the different diagnostic methods

To make objective estimates of the costs associated with the different diagnostic methods, we will collect data on the cost of the materials used as well as the time required to prepare and examine stool samples for the different stool-based diagnostic methods.

### Assessing costs of reagents and materials

Detailed pricing information for the list of materials needed to perform Kato-Katz thick smear and Mini-FLOTAC will be obtained from the local PI. The costs for the materials needed for the FECPAK^G2^ method will be obtained from the manufacturer (Techion Group Ltd.) and is expected to be the same for all four study sites. A list of materials included in the cost calculation for the Kato-Katz thick smear and Mini-FLOTAC method is provided in S11 Info. The costs associated with molecular analysis of the samples will include the cost for preservation and shipment of the stool samples as well as the laboratory materials used to perform DNA extractions and qPCR.

### Timing of diagnostic methods

Timers will be provided to each laboratory technician to measure the time needed to perform the different steps of each of the diagnostic methods. For all egg counting methods, the time taken to complete each step will be measured. In addition, the time needed for data entry and drafting a report will be recorded. The protocols of the egg counting methods include more details on the different timing steps (S3–S5, S8 and S10 Info).

### Data management

All data collected during the studies will be recorded in specifically designed record forms (S12 Info). The original results written down on the paper documents will be scanned and stored digitally. This data will later be entered into customized Excel-files by two separate individuals (S13–S15 Info). After completion of the data entry, the files of both data entry clerks will be compared for discrepancies (S16 Info). Potential mismatches will be highlighted and the true values verified using the scanned original record form.

### Study management and coordination

The PIs from each site are responsible for acquiring ethical approval by their local Institutional Review Board (IRB) and conducting the trial procedures as described in the original study protocol and study SOPs. The studies in the different countries will be coordinated by the project PI and the Starworms Coordinating Team at Ghent University. One week prior to the start of each study, a member of the Starworms Coordinating Team will visit the study site. Local team members will be informed on the study design, familiarised with the different study documents and receive both theoretical and practical training on how to perform different egg counting methods according to the Starworms SOPs. The Starworms staff member will remain on-site for at least 7 days after the start of the trial to ensure SOP adherence and to solve any issues that might arise.

### Statistical data analysis

After data collection and quality control, all data will be combined in a final, protected dataset for statistical analysis. After finishing work package 1, this dataset will be made available on the Starworms website (www.starworms.org). All statistical analysis will be performed in R (R Development Core Team, 2016).

### Assessment of the impact of previously conducted PC in reducing STH morbidity

We will evaluate both the prevalence and intensity of each different STH species in each of the four different study sites. The percentage of individuals included in the different classes of infection intensity will be reported in order to assess the efficacy of the PC intervention conducted until then in eliminating STH infection of moderate and heavy intensity.

### Assessment of the equivalence of egg reduction rates measured by Kato-Katz thick smear, Mini-FLOTAC and FECPAK^G2^

We will report the efficacy of a single oral dose of 400 mg ALB separately for *A*. *lumbricoides*, *T*. *trichiura* and hookworms, and for each FEC method by means of ERR, using the formula below:ERR=100%×(arithmeticmean(FECatbaseline)−arithmeticmean(FECatfollow-up))/(arithmeticmean(FECatbaseline))

A bootstrap analysis will be used to determine the corresponding 95% confidence intervals (95% CI) for each egg counting method and for the pair-wise differences in ERR across diagnostic methods. A permutation test will be used to assess the equivalence in ERR between a duplicate Kato-Katz thick smear, and a single Kato-Katz thick smear, Mini-FLOTAC and FECPAK^G2^. Tukey’s method will be applied for multiple comparison between methods. In addition, the agreement between a duplicate Kato-Katz thick smear and the other egg counting methods in the assignment of drug efficacy into ‘satisfactory’, ‘doubtful’ and ‘reduced’ will be evaluated by Fleiss’ kappa statistic (κ_Fleiss_). This classification of the drug efficacy will be based on the criteria recently proposed by the WHO (Table 4) [27]. The value of this statistic indicates a slight (κ_Fleiss_ <0.2), fair (0.2 ≤ κ_Fleiss_ <0.4), moderate (0.4 ≤ κ_Fleiss_ <0.6), substantial (0.6 ≤ κ_Fleiss_ <0.8) and an almost perfect agreement (κ_Fleiss_ ≥ 0.8).

**Table 4 pntd.0006912.t004:** Classification of the efficacy of a single oral dose 400 mg albendazole against STH.

STH	Satisfactory	Doubtful	Reduced
***Ascaris***	ERR ≥ 95%	85% ≤ ERR < 95%	ERR < 85%
***Trichuris***	ERR ≥ 50%	40% ≤ ERR < 50%	ERR < 40%
**Hookworms**	ERR ≥ 90%	80% ≤ ERR < 90%	ERR < 80%

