### General design of the field trials

A series of drug efficacy trials will be performed in four STH endemic countries (Brazil, Ethiopia, Lao PDR and Tanzania). These trials will be designed to assess the efficacy of a single oral dose of 400 mg ALB against STH infections in SAC by a variety of stool-based diagnostic methods. At the start of each trial, schools will be visited by the local principal investigator (PI) and a team of field officers, who will explain the planned trial and sampling method to the parents and teachers and the children. At baseline, SAC will be asked to provide a fresh stool sample. All children that meet all inclusion criteria and none of the exclusion criteria (see Table 1) will be enrolled in the study. They will be treated with a single oral dose of 400 mg ALB under supervision. The ALB to be used in the different studies is manufactured by GlaxoSmithKline and donated to WHO and originates from the same production batch (Batch Nr: 335726). All collected stool samples will be processed to determine the fecal egg counts (FECs; expressed in eggs per gram of stool (EPG)) for each STH using Kato-Katz thick smear (single and duplicate), Mini-FLOTAC and FECPAK^G2^. During baseline evaluation, only stool samples found to contain at least 13 eggs on duplicate Kato-Katz or at least 15 eggs on Mini-FLOTAC for at least one of the three STHs will be preserved for further molecular analysis. Fourteen to 21 days after drug administration, a second stool sample will be collected from all the children that were excreting eggs of any STH at baseline based on Kato-Katz thick smear and Mini-FLOTAC. Stool samples will be examined by Kato-Katz thick smear (single and duplicate), Mini-FLOTAC and FECPAK^G2^. All follow-up samples will be preserved for further molecular analysis. To gain insights into the operational costs for assessing drug efficacy, the time to process stool with Kato-Katz thick smear, Mini-FLOTAC and FECPAK^G2^, and the time needed to enter data and to draft reports will be assessed. The different steps of the trials are schematized in Fig 1.

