### Sample size calculation

A sample size was calculated to test the alternative hypothesis that FECPAK^G2^, Mini-FLOTAC and single Kato-Katz thick smear provide equivalent drug efficacy results measured by ERRs compared to a duplicate Kato-Katz thick smear. Given the differences in drug efficacy of ALB across the STH species [15, 21] (*Ascaris*: ~99%, hookworms: ~96%, *Trichuris*: ~65%), a level of equivalence that is acceptable for *Trichuris* may not be acceptable for *Ascaris*. Therefore, a species-specific level of equivalence was used. For *Ascaris* the level of equivalence was set at 2.5-point percentage, for hookworms and *Trichuris* the level of equivalence was set at 5.0 and 10 point percentage, respectively. Both type I and II errors were set at 0.05.

To calculate the corresponding sample size for each of the STH species, we performed a simulation study. This simulation study considered (i) variation in ERR and baseline FECs across and within STH species, (ii) variation in FECs introduced by the egg counting process, (iii) the paired ERR results across egg count methods, and (iv) a post-hoc correction for a pair-wise comparison. Based on the simulation, at least 110, 100 and 12 complete cases are required for *Trichuris*, hookworm and *Ascaris*, respectively. A detailed description of the sample size calculation is available in the supplementary information (S1 Info).

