### Provide proof-of-principle for qPCR to assess infection intensity and drug efficacy by means of reduction in GE

The efficacy of a single oral dose of 400 mg ALB will be reported separately for *A*. *lumbricoides*, *T*. *trichiura* and hookworms by means of genome equivalent reduction rate (GERR), using the formula below: GERR = 100% x (arithmetic mean(GE at baseline)–arithmetic mean (GE at follow-up)) / (arithmetic mean (GE at baseline)).

The corresponding 95% CI for GERR will be determined by bootstrap analysis (10,000 iterations). A permutation test will be used to assess the equivalence in drug efficacy between a duplicate Kato-Katz thick smear by means of ERR and qPCR by means of GERR for each of the STH species separately. The same level of equivalence will be applied as described in section 4.8.1. In addition, the agreement between a duplicate Kato-Katz thick smear and qPCR in the assignment of drug efficacy into ‘satisfactory’, ‘doubtful’ and ‘reduced’ will be evaluated by κ_Fleiss_ statistic.

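### Fleiss' kappa on the efficacy class can be undefined, or read as slight at 92% agreement, when units share one class; cross-tabulation and raw agreement should lead

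*Protocol article*

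**What the plan says.** In the protocol article's section on equivalence of egg reduction rates, efficacy is reported by species "and for each FEC method by means of ERR, using the formula below". The formula is a ratio of arithmetic means over children, so each method gives one ERR per group of children and species. Table 4 turns that ERR into satisfactory, doubtful or reduced.

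After the bootstrap intervals and the equivalence test, the section adds that "the agreement between a duplicate Kato-Katz thick smear and the other egg counting methods in the assignment of drug efficacy into" these three classes "will be evaluated by Fleiss’ kappa statistic". Values below 0.2 are read as slight, 0.6 to below 0.8 as substantial, and 0.8 or more as almost perfect. The proof-of-principle section for qPCR repeats the comparison for the genome equivalent reduction rate (GERR): agreement with duplicate Kato-Katz "will be evaluated by κ_Fleiss_ statistic".

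Classification of individual children is a separate matter. Table 3, under Pyrosequencing, is "based on the individual egg reduction rate (iERR") and serves to select samples. Table 4 uses the group ERR.

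The design section describes drug efficacy trials in four countries. The article does not say whether the unit for kappa is the trial, the school or a pooled group, nor whether methods are compared in pairs or jointly.

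**The concern.** Kappa corrects observed agreement for the agreement expected from the marginal class frequencies. When nearly all units fall in one class, expected agreement approaches 1. The coefficient then says more about how the classes are distributed than about how well the methods match.

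Both conditions that make this serious are plausible here. A class attached to a group ERR gives few units, and the planning ERRs all lie above the satisfactory cut-offs.

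At stake is the message about whether FECPAK^G2^, Mini-FLOTAC, a single Kato-Katz smear and qPCR lead to the same WHO efficacy class as duplicate Kato-Katz. Followed as written, the statistic and scale can give no value for perfect agreement, or the lowest label for near-perfect agreement.

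**Working it through.** The article states no kappa value, number of units or precision, so there is no figure to reproduce.

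**Inputs**
- Four trials (General design of the field trials) and three species groups reported separately (equivalence section). If the unit is the trial: 4 per species, 4 x 3 = 12 in all. Pooling sites would leave 3; using schools would give more.
- Planning ERRs (Sample size calculation, the sentence starting "Given the differences in drug efficacy of ALB across the STH species") against the Table 4 satisfactory cut-offs:

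| Species | Planning ERR | Cut-off | Margin (points) |
|---|---|---|---|
| *Ascaris* | ~99% | 95% | 4 |
| Hookworms | ~96% | 90% | 6 |
| *Trichuris* | ~65% | 50% | 15 |

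**Formula.** Fleiss' kappa = (Po - Pe)/(1 - Pe). Po is the mean agreement over units; Pe is the sum of squared class proportions over all ratings. With two methods, N units give 2N ratings.

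**Two methods, all concordant units satisfactory**
- Full agreement, any N: Po = 1, Pe = 1, kappa = 0/0.
- 12 units, one discordant: Po = 11/12 = 0.917; Pe = (23/24)² + (1/24)² = 0.920; kappa = -0.043.
- 4 units, one discordant: Po = 0.75; Pe = (7/8)² + (1/8)² = 0.781; kappa = -0.143.
- In general, one discordant unit among N gives -1/(2N - 1). With N = 40, agreement is 97.5% and kappa is -1/79 = -0.013, so more units alone do not cure the problem.

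**Four methods jointly**, 12 units, one deviating rating: Po = (11 + 0.5)/12 = 0.958; Pe = (47/48)² + (1/48)² = 0.959; kappa = -0.021.

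**Two methods, 12 units, one concordantly doubtful**
- No discordance: Pe = (22/24)² + (2/24)² = 0.847; kappa = 1.00.
- One discordant (satisfactory/doubtful), ten concordantly satisfactory: Po = 0.917; Pe = (21/24)² + (3/24)² = 0.781; kappa = 0.135/0.219 = 0.62.
- With two or three concordantly doubtful units and one discordant: 0.75 and 0.80 (0.798 unrounded).

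So 11 of 12 agreeing gives -0.04 (slight) or +0.62 (substantial), depending on the class of one unit on which the methods agree.

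**How likely is the one-class case?** The article gives no between-site spread. As an assumption only, take true site ERRs as independent and normal around the planning values. The chance that all 12 are satisfactory is then:

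| Assumed SD (*Ascaris*/hookworm/*Trichuris*, points) | Chance |
|---|---|
| 1/3/5 | 0.907 |
| 2/4/10 | 0.525 |
| 2/5/15 | 0.280 |

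**The case against.** The unit is never named, so a reader might infer that the plan commits to 4 units per species. It does not. Recruitment runs through schools, pooling across sites is possible, and a full protocol or analysis plan may settle the matter. This stands, and the 12-unit figures are therefore conditional. It does not remove the problem, which persists with 40 units if all concordant ones are satisfactory.

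A reader might also infer that kappa must come out undefined or negative. The documents do not support that either. Both results need every concordant unit to be in one class. The Discussion says the sites were chosen for varying drug pressure and hence possibly different efficacy, and the planning ERRs are approximate species-level values, not forecasts by site or method. One concordantly doubtful unit gives 1.00 under full agreement and +0.62 with 11 of 12 agreeing. This stands as a limit on the claim. It also shows the weakness, since the label then turns on whether a site has low efficacy.

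Finally, kappa is an addition to ERRs with intervals, intervals for pairwise differences, and an equivalence test. Readers could derive each class from the reported ERR and Table 4. This too stands: the point concerns a secondary summary.

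**Conclusion.** The point holds in conditional form. The article fixes a statistic and a verbal scale that can mislead on its own planning figures. If the unit is the trial and all concordant units are satisfactory, kappa is undefined under full agreement, -0.04 with 11 of 12 agreeing and -0.14 with 3 of 4 agreeing; both negative values would be called slight. With one concordantly doubtful unit, the same 92% agreement is called substantial.

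This rests on Table 4 classifying a group ERR, which the formula and the separate Table 3 support; on the trial as unit, which is inferred; and on one dominant class, which the planning ERRs suggest but site differences may prevent. A reader might infer that the equivalence conclusions or the sample size are undermined. They are not: neither uses kappa. The change is worth making because the study aims to recommend methods for monitoring drug efficacy, and a wrong label on class agreement would bear on that.

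**What to change.** In the equivalence section and the qPCR proof-of-principle section:

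1. Name the unit of classification (for example site by species) and say whether methods are compared in pairs with duplicate Kato-Katz or jointly.
2. Make the cross-tabulation of Table 4 classes, and the number of units given the same class, the main agreement result.
3. For each site-by-species unit, add the proportion of paired bootstrap resamples, with the same children for both methods, in which the two methods give the same class. For qPCR, draw these from children who have both results at both visits.
4. Drop the verbal scale. Report kappa, if at all, as a supplement and only when more than one class occurs.
5. Describe any interval on the count over 12 units as approximate, because species within a site are not independent. For scale, the exact binomial interval for 11 of 12 is about 62% to 99.8%.

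The cost is analysis wording and a small extension of the bootstrap already planned. No extra data are needed.
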